**Trial registration number:**

ACTRN12615001160527; pre-results.

Strengths and limitations of this studyOne of the largest randomised controlled trials assessing mindfulness interventions and the largest involving students, to date.A pragmatic design evaluating the provision of a service, intended to inform university student welfare policies in the global context of massively increasing participation in higher education.Interdisciplinary team and horizontal co-production of research question and study design between researchers and stakeholders.Study design assesses the effectiveness of mindfulness (ie, whether it produces the expected results under ‘real-world’ settings), but does not test its efficacy (ie, whether mindfulness produces the expected results under ideal circumstances, such as perfect course attendance), or determine its specific effects.

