Process measures will involve: (1) registering attendance at mindfulness courses (register taken) and asking why sessions were missed (routine practice for UCS); (2) asking students whether they did their mindfulness homework during the course and how much they have practised after the course, including whether they became members of the Mindfulness Society; (3) for students who abandon the study (ie, fail to complete questionnaires or contact us saying they wish to quit the study), information on why they have done so will be requested; (4) participants in the control group will be asked whether they have practised mindfulness elsewhere during the follow-up period.

Apart from the baseline measurements outlined in table 1, the following baseline data will be collected in order to compare the sample with the student population, and to run subgroup analyses: (1) students' prior experience with meditation and mindfulness; (2) demographic data provided by the student registry (eg, disability, ethnicity, socioeconomic classification). All baseline data will be collected before randomisation.

Questionnaires will be web-based. Privacy issues related to accessing student records and collecting data from smartphone sensors were explored in a focus group with students who completed mindfulness courses taught before the trial. Students felt these methods were acceptable.

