### Statistical methods

The primary analysis will consist of an intention-to-treat analysis comparing the primary outcome, CORE-OM during the examination period, between arms adjusted for baseline scores, routine demographics and timing of receipt of intervention relative to examinations (as some will have done the course during Michaelmas 2015 and others during Lent 2016). Multiple imputation will be used as long as there are <40% missing data in the corresponding variable to ensure validity of imputations and will be applied only to variables with expected missing completely at random and missing at random patterns (ie, when there are no reasons to think that the pattern may be missing not at random). This imputation will take account of other CORE-OM data points and routinely collected demographics. We will also conduct a per-protocol analysis (minimum dose assumed to be 50% attendance of sessions^24^) excluding individuals in the control group who have engaged in meditation elsewhere during the follow-up period preceding outcome measurement.

Outcomes measured at three time points (CORE-OM, WEMWBS and altruism, measured at postintervention, examination period and 1-year follow-up) will be analysed using a repeated measures design with a treatment by time interaction term to study their trajectories through the academic year and to determine whether differences (ie, intervention effects) were consistent over time. Repeated measures analyses will also be performed with ecological momentary assessment data to study outcome trajectories, pattern changes during the examination period and differences between arms.

CORE-OM and WEMWBS data will be combined to explore the broader spectrum of distress/well-being if taken as a continuum.^25^ Subscales of the CORE-OM (subjective well-being, problems symptoms, functioning, risk/harm) will also be explored as secondary outcomes, and results reported with and without correction for multiple testing. Multilevel models will be used to assess academic degrees and academic rankings as any student may sit more than one examination.

The following predefined subgroup analyses will be conducted on the primary outcome by using interaction tests:^26^

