### Consent

After reading the participant information sheet, students will be able to consent online or in person (a copy of the consent form is available as an online supplementary file). The electronic and paper-based information sheets and consent forms will have the same content. They will clearly state eligibility criteria and request students to self-assess whether they meet them. They will also list other mental health support resources (eg, University Counselling Service) within and outside the University for those who do not wish or cannot take part in this study.

Information sessions will be set up in central locations on different days where a member of the research team will distribute participant information sheets. They will give plenty of time for students to read them and ask all the questions they need. They will also be able to take the information sheet with them and come back later or use the website to consent. The mindfulness teacher will be either present at the sessions or reachable by phone and email for students to ask questions about the course.

The online consent will be programmed in Qualtrics and participants' consents will be recorded in a secure database. An ‘I agree’ button will allow participants to continue answering baseline questionnaires, those who do not consent will not be able to continue answering, so no personal information about them will be recorded online before they consent. If a student reads the participant information on the website and has questions, they will be able to phone and email the research team, or attend the information sessions. They will be emailed a copy of the consent for their records.

Students in their final year have a 50% chance of assignment to the control group and may not be able to receive the mindfulness course in the following year unless they stay on for another degree. This issue was explored in the focus group with students and it did not raise any significant concerns. However, this circumstance will be made clear in the participant information sheet for last year students to make an informed decision on whether to take part in the study. In any case, participants randomised to the control group will not be requested to avoid learning mindfulness elsewhere, and a list of resources to do so will be offered in the study website.

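### The per-protocol analysis excludes on a different post-randomisation behaviour in each arm, so it is not a randomised comparison and should be labelled so, with a complier analysis beside it

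*Protocol article*

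**What the plan says.** Under Statistical methods, the primary analysis is by intention to treat: "The primary analysis will consist of an intention-to-treat analysis comparing the primary outcome, CORE-OM during the examination period, between arms", adjusted for baseline score, demographics and timing of the course. A per-protocol analysis is added. For the intervention arm the rule is "minimum dose assumed to be 50% attendance of sessions", which is four of eight. The text does not say outright that students below this are dropped, but a minimum dose in a per-protocol analysis implies it. For the control arm the rule is "excluding individuals in the control group who have engaged in meditation elsewhere during the follow-up period preceding outcome measurement", with no dose threshold.

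Outcomes and data collection shows that the two behaviours are measured differently. Attendance comes from a class register. For the control arm, "participants in the control group will be asked whether they have practised mindfulness elsewhere during the follow-up period". The Consent section adds that "participants randomised to the control group will not be requested to avoid learning mindfulness elsewhere", and that the study website will list resources for doing so. The strengths and limitations list says that the design "does not test its efficacy (ie, whether mindfulness produces the expected results under ideal circumstances, such as perfect course attendance").

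**The concern.** Randomisation makes the arms comparable as allocated. This analysis keeps intervention students according to what they did about the course, and controls according to what they did about meditation elsewhere. Controls who would have been low attenders cannot be identified, so they stay in. Intervention students who would have sought meditation elsewhere had they been controls cannot be identified either.

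The protocol gives reasons to think that both behaviours may carry information about distress. Under Intervention, students who miss a session are emailed to see whether a bad experience with mindfulness lies behind it. Under Data monitoring and adverse events, early experiences in the course are described as possibly distressing. Dropping low attenders could therefore drop those for whom the course went badly. Control meditation is foreseen and self-selected.

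At stake is the only comparison in the protocol aimed at the effect of attending the course. Nothing in the text marks it as non-randomised, and the trial is meant to inform university policy.

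**Working it through.** **Inputs from the protocol.** Target difference 0.3 SD; SD 0.59 points, so 0.3 × 0.59 = 0.177 points; 275 per arm with 20% loss, so 275 × 0.8 = 220 evaluable per arm. The protocol gives no figure for the per-protocol analysis, so there is none to reproduce. It also gives no attendance rate, control meditation rate or relation of either to distress. Those below are assumptions.

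**Step 1: intervention arm alone.** Bias = (1 − p) × Δ, where p is the share reaching 50% attendance and Δ is the outcome difference between would-be attenders and non-attenders.
- p = 0.8, Δ = 0.2 SD: 0.2 × 0.2 = 0.04 SD, and 0.04/0.30 = 13% of target.
- p = 0.6, Δ = 0.4 SD: 0.4 × 0.4 = 0.16 SD, and 0.16/0.30 = 53% of target.

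**Step 2: both exclusions, baseline-adjusted, no true effect.** Each scenario simulated 2,000,000 students, with a baseline-to-examination correlation of 0.5. Low attendance and control meditation were each allowed to correlate with higher distress. Negative values are spurious benefit.

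| Reach 50% | Controls who meditate | Correlation, low attendance | Correlation, control meditation | Per-protocol estimate (SD) |
|---|---|---|---|---|
| 65% | 10% | 0.4 | 0.4 | −0.12 |
| 65% | 10% | 0.2 | 0.2 | −0.06 |
| 65% | 10% | 0.4 | 0 | −0.17 |
| 50% | 20% | 0.4 | 0.4 | −0.14 |
| 80% | 5% | 0.4 | 0.4 | −0.07 |
| 65% | 10% | 0 | 0 | 0.00 |

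Hand check of the first row. Baseline leaves 1 − 0.5² = 0.75 of the variance unexplained. With φ the normal density at the cut-off:
- intervention arm: −0.75 × 0.4 × 0.370/0.65 = −0.171;
- control arm: +0.75 × 0.4 × 0.1755/0.90 = +0.0585;
- sum: about −0.11, against −0.115 simulated.

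The two terms have opposite signs, so removing distressed controls offsets part of the intervention-arm bias. If low attenders were the less distressed students, the first term would change sign.

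The CACE (intention-to-treat effect divided by p) was 0.00 in every one of these scenarios.

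**Step 3: true effect of −0.30 SD in those reaching the dose, p = 0.65, correlations 0.4, 10% of controls meditating.**
- Low attenders gain nothing: intention-to-treat 0.65 × 0.30 = 0.195; CACE 0.195/0.65 = 0.30 (simulated −0.29). Per-protocol −0.41.
- Low attenders gain half: (0.195 + 0.35 × 0.15)/0.65 = 0.2475/0.65 = 0.38. Per-protocol −0.42.
- The meditating controls gain 0.30: (0.195 − 0.10 × 0.30)/0.65 = 0.165/0.65 = 0.25. Per-protocol −0.41.

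**Step 4: precision.** The standard error of the CACE is about 1/p times that of intention-to-treat: 1.25, 1.54 and 2.0 at p = 0.80, 0.65 and 0.50. With 220 per arm and no covariate adjustment, the intention-to-treat standard error is √(2/220) = 0.095 SD, so the CACE has 0.119, 0.147 and 0.191 SD.

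**The case against.** Several points on the other side are fair.

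- **Little rests on this analysis.** The primary analysis is intention-to-treat, baseline-adjusted and done blind to arm, and the protocol disclaims efficacy under perfect attendance. This stands, and it limits the weight of the point.
- **Per-protocol beside intention-to-treat is conventional, arm-specific rules are hard to avoid when one arm is offered a course, and further analyses may sit in an analysis plan not shown.** The absence of a CACE is indeed no defect. What can be criticised is the exclusion rule, which the protocol already fixes.
- **Selection may be mild.** Everyone must expect to attend at least seven sessions, and missed sessions can be made up in another group that week. This narrows selection but does not remove it.
- **The CACE has its own weakness.** It assumes that attending fewer than half the sessions brings no benefit, which is doubtful for a cumulative skills course with home practice. Step 3 shows it at −0.38 or −0.25 against a true −0.30. With meditating controls retained, it also estimates a slightly different contrast: the course against usual provision including self-sought practice. A reader might infer that it answers the question free of bias; it removes the selection bias only.

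Two other inferences are tempting and unsupported. One is that students with prior meditation experience are removed from the control arm only. The rule concerns meditation during follow-up; prior experience is a separate baseline variable with its own subgroup test. The other is that a single dose rule could define exposure in both arms from data already planned. The protocol says only that controls are asked if they practised, not how much.

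**Conclusion.** The point holds in a limited form. As written, the per-protocol analysis compares groups that are no longer randomised, and it can show an effect when there is none. Across the assumed patterns the bias is roughly 0.04 to 0.17 SD (0.17/0.30 = 57% of target at the upper end), or 0.024 to 0.100 CORE-OM points (0.04 × 0.59 and 0.17 × 0.59). Baseline adjustment does not remove it when attendance depends on later distress. It is zero if neither behaviour is related to distress.

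The documents do not support calling the bias certainly favourable or giving it a definite size, because they contain no compliance figures and the two exclusions can pull in opposite directions. Nor do they support any doubt about the primary result on this ground.

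**What to change.** Keep intention-to-treat as primary. State that the per-protocol comparison is non-randomised and descriptive.

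Add a CACE for the examination-term CORE-OM by two-stage least squares: randomised arm as instrument; exposure defined as attending at least 50% of course sessions, from the register; the same baseline covariates as the primary model. Retain all controls and code them as not having attended the course.

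State the assumptions: no benefit below 50% attendance, and monotonicity. The latter is plausible because controls are offered the course only a year later. Add sensitivity analyses that allow partial benefit in low attenders and benefit in controls who report practising elsewhere.

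The cost is wording, one standard model and its sensitivity analyses. The main CACE uses only data already planned. A dose threshold for control practice, if wanted, may need an extra question. The statistical price is the wider confidence interval in step 4 and reliance on the exclusion restriction.

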## Abstract

**Introduction:**

Levels of stress in UK university students are high, with an increase in the proportion of students seeking help in recent years. Academic pressure is reported as a major trigger. Mindfulness training has been shown to reduce stress and is popular among students, but its effectiveness in this context needs to be ascertained. In this pragmatic randomised controlled trial, we hypothesise that the provision of a preventative mindfulness intervention in universities could reduce students' psychological distress during the examination period (primary outcome), improve their resilience to stress up to at least 1 year later, reduce their use of mental health support services and improve academic performance.

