### Outcomes and data collection

Several outcomes will be measured and compared between mindfulness and control groups to assess the effects of the course. The primary outcome will be a self-reported global measure of psychological distress assessed during the examination term, the most stressful period of Cambridge students' academic year. Secondary outcomes are exploratory assessments that may help to describe mindfulness' effects in more focused ways. Outcomes are listed in table 1.

**Table 1 BMJOPEN2016012300TB1:** MSS study outcomes

Outcome	Source/measure	Variable type	Collection points
Use of mental health services	Self-reported	Nominal	One-year follow-up
Use of University Counselling Service	Routinely collected	Nominal	Baseline, 1-year follow-up
Perceived impact of problems on academic performance	Self-reported	Ordinal	Examination term
Examination grades and rankings	Routinely collected	Ordinal	Examination term
Special circumstances requests for examinations	Routinely collected	Nominal	Examination term
Inability to sit examinations (intermissions and degrading)	Routinely collected	Nominal	Examination term
Psychological distress	Self-reported: CORE-OM	Treated as interval	Baseline, postintervention, examination term, 1-year follow-up
Well-being	Self-reported: WEMWBS	Treated as interval	Baseline, postintervention, examination term, 1-year follow-up
Altruism	Behavioural	Ordinal	Postintervention, examination term, 1-year follow-up
Coping	Self-reported	Ordinal	Baseline (Lent), examination term
Physical activity	Behavioural (sensor)	Ratio	Baseline (Lent), examination term
Sleep times	Behavioural (sensor)	Ratio	Baseline (Lent), examination term

CORE-OM, Clinical Outcomes in Routine Evaluation Outcome Measure; MSS, Mindful Student Study; WEMWBS, Warwick-Edinburgh Mental Well-being Scale.

Psychological distress will be measured using the Clinical Outcomes in Routine Evaluation Outcome Measure (CORE-OM), a 34-item generic questionnaire which was designed to assess efficacy and effectiveness across multiple disciplines offering psychological therapies, and has been widely used with UK university students. It is scored on a five-point scale ranging from 0 (not at all) to 4 (most or all the time). The total score range is 0–136; this is usually divided by number of completed items to form a total mean score. CORE-OM has good convergent validity, internal and test–retest reliability and sensitivity to change.^14^

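### The planned grade comparison is in effect conditional on sitting examinations, a post-randomisation event that the trial itself compares between arms

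*Protocol article*

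**What the plan says.** All references are to the protocol article.

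- **Grades.** Table 1 lists "Examination grades and rankings" as a routinely collected, ordinal outcome in the examination term. Statistical methods gives the model and its reason: "Multilevel models will be used to assess academic degrees and academic rankings as any student may sit more than one examination".
- **Not sitting.** In the same table, the entry beginning "Inability to sit examinations (intermissions and degrading" is a separate nominal outcome for the same term, also from routine records. The section introduces the table with: "Several outcomes will be measured and compared between mindfulness and control groups to assess the effects of the course".
- **Missing data.** Statistical methods says imputation will be "applied only to variables with expected missing completely at random and missing at random patterns", glossed as "when there are no reasons to think that the pattern may be missing not at random". The variable must have less than 40% missing. The named predictors are the other CORE-OM time points and demographics.
- **Status and aim.** Outcomes and data collection says: "Secondary outcomes are exploratory assessments that may help to describe" the effects of mindfulness in more focused ways. The abstract hypothesises that provision could "reduce their use of mental health support services and improve academic performance". The fourth objective likewise names academic performance.
- **Students without examinations for another reason.** The subgroup list in Statistical methods notes that some degrees have no examinations in that term.

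**The concern.** A grade exists only for a student who sits. Sitting comes after randomisation, and the trial examines it as a possible effect of the course. If the two arms differ in who sits, the students with grades in one arm are no longer comparable with those in the other, even though the arms were comparable at randomisation.

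The two academic outcomes can then work against each other. Suppose the course keeps in the examinations some students who would otherwise have intermitted, and these students score below average. Their grades enter the intervention arm, while their counterparts in the control arm contribute nothing. A benefit on sitting would show up as a small apparent harm on grades. The article ties academic performance to an objective, and says that the evaluation is to inform the University's decisions about provision, so the grade result may be read on its own.

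**Working it through.** **Step 1: set the rules side by side.** The grade model is justified by the number of examinations a student sits, so a student with none supplies no record. A mixed model of the observed grades is valid only if the absent grades are missing at random given what is in the model. The imputation rule excludes variables where there is reason to suspect otherwise, and being unable to sit is plausibly such a reason. The rule also stands in the paragraph on the primary analysis, and its named predictors do not include academic information. Nothing in the article links the grade outcome to the inability-to-sit outcome.

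**Step 2: inputs.** The article gives no non-sitting rate, no grade deficit and no expected grade effect, so there is no figure of the plan to reproduce here. Its 550 students (275 per arm) are for CORE-OM, and 275 is used below only to scale a standard error. Everything else is assumed and shown as a range.

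**Step 3: simple model with no true effect on grades.** Let a proportion p0 of students be vulnerable, with grades delta SD below the rest. In the control arm none of them sits. In the intervention arm only p1 do not sit, so p0 - p1 are retained. The false difference (intervention minus control) among sitters is

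-(p0 - p1) × delta / (1 - p1)

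| Control vs course not sitting | delta = 1 | delta = 1.5 |
|---|---|---|
| 4% vs 2% | -0.02/0.98 = -0.020 | -0.031 |
| 6% vs 3% | -0.03/0.97 = -0.031 | -0.046 |
| 10% vs 5% | -0.05/0.95 = -0.053 | -0.079 |

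**Step 4: a different selection model as a check.** Give each student a standard normal latent risk. Those above the threshold t that leaves a proportion p above it do not sit, and risk has correlation rho with low grades. With phi the standard normal density, the mean grade of sitters is rho × phi(t)/(1 - p), and the bias is the intervention value minus the control value.

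| Control vs course not sitting | rho = 0.3 | rho = 1 |
|---|---|---|
| 2% vs 1% | -0.007 | -0.022 |
| 5% vs 2.5% | -0.015 | -0.049 |
| 10% vs 5% | -0.026 | -0.086 |

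With rho = 0 the bias is zero. With rho = -0.3 the sign reverses, giving +0.007 to +0.026 over the same rates.

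**Step 5: scale.** For a simple two-arm comparison with 275 per arm, the standard error is sqrt(2/275) = 0.085 SD. In Step 3 the pull runs from 0.020/0.085 = 0.24 to 0.079/0.085 = 0.93 of a standard error. In Step 4 it reaches about one standard error only at 10% vs 5% with rho = 1.

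**The case against.** The strongest objection is that the article never says that grades are compared only among sitters. The sentence on multilevel models explains why repeated examinations need them; it defines no analysis population. How to treat ungraded students in an exploratory outcome is ordinary content for an analysis plan, which is not shown. This stands in part: silence alone would be no finding. But the article does commit to a per-examination model and to a restrictive imputation rule, and together these lead to a comparison among sitters unless something further is added.

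Three stronger readings are tempting, and the documents do not support them.

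- A reader might infer that the trial expects the course to reduce intermission. Table 1 lists inability to sit without a direction, and the hypotheses and objectives do not mention intermission or degrading.
- A reader might infer that the bias always runs against a course that works. That needs the course to reduce non-sitting and the retained students to score below average. Neither is stated, and Step 4 shows zero or reversed bias under other assumptions.
- A reader might add the students whose degree has no examination that term. They differ by a baseline feature, balanced in expectation by randomisation. They lower the observed rate of inability to sit but do not bias the grade contrast.

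It is also fair to say that the trial collects inability to sit and special circumstances requests, so a difference in sitting would be visible to a reader who looks at both. Finally, ranking every intermission below every grade is a value judgement, and it needs one result per student where the article plans for several examinations. Both remarks stand and limit the remedy.

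**Conclusion.** The point holds as a limited one. The planned grade contrast conditions on an event that the trial itself tests as an effect of the course, so it lacks the protection of randomisation if the arms differ in who sits. The likely distortion is small: about -0.02 to -0.08 SD under the Step 3 assumptions, which is below one standard error. The size rests wholly on assumed rates and deficits, and the sign on the two conditions named above. The outcome is exploratory, and the primary CORE-OM comparison is not touched. This is a cheap improvement in clarity, not a flaw that threatens the trial's main conclusion.

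**What to change.** 1. Define the academic-outcome population from baseline information as students in both arms due to sit examinations in the 2016 examination term. Use it as the common denominator for grades, inability to sit and special circumstances requests.
2. Keep the multilevel model, label it conditional on sitting, and report it beside inability to sit by arm.
3. Add a sensitivity analysis over everyone in that population: one overall ordinal result per student, with not sitting (intermission or degrading) as the lowest category, compared by a proportional-odds or rank method. State in advance how several examinations are reduced to one result.

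The cost is one extra analysis of registry data already planned. The drawback is that the combined scale mixes grade with intermission, which is why it should be a sensitivity analysis with both components shown next to it.

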### Trial design

The study will be a pragmatic randomised controlled evaluation with two parallel arms and a one-to-one allocation rate testing the superiority of mindfulness training provision to no provision. University of Cambridge students will be randomised to joining a mindfulness course during the term they are starting plus mental health provision as usual (PAU), or to PAU alone. PAU comprises access to individual counsellors, mental health advisors and psychiatrists at the University of Cambridge Counselling Service (UCS), as well as access to welfare staff in the University colleges (this provision varies across colleges, but can include college nurse, counsellor, welfare officer or tutor) and National Health Services (NHS). Those allocated to PAU alone will be offered a mindfulness course 1 year later, providing they are still students at the University.

The mindfulness intervention was offered for two terms before study initiation; this allowed the intervention to become established before evaluating it, and provided feasibility and acceptability data. The present proposal is partly based on the experience during those two terms. Interest in the courses doubled teaching capacity. An opportunistic randomised evaluation was therefore considered reasonable.

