By degree, as most have examinations during the examination term but some do not;By year of study, to explore whether results differ for last year students, a different subpopulation as control group final year students will not be offered mindfulness a year later;By baseline CORE-OM: those initially worse may drive change;By gender: there is evidence of differential impact;^10^By amount of home practice during and after course in intervention group participants;By prior meditation experience (prior 8-week course or +50 hours spent meditating in the past—an 8-week course translates into 10–50 hours) as only novices may experience a change.

In order to assess how our sample compares against the student population in the UK, demographic and normative well-being/distress data will be obtained from the literature and compared with baseline values in our sample. A comparison of our baseline data with the profile of students attending the University Counselling Service will also be performed where possible to evaluate where our sample lies in the range between community and clinical student samples.

All statistical analyses will be conducted at an α level of p=0.05 (two-sided). Linear mixed models will be used for the analyses. Assumptions will be tested and diagnostic plots will be explored to assess model fit. Descriptive statistics for continuous variables will be summarised using mean/SD and median/IQR. Discrete variables will be summarised by proportions.

It is expected that the clustering effect will be negligible: although this is a group intervention, the work is highly personal, all the courses are taught by the same teacher, each course includes students from different colleges and courses, and the ‘session hopping’ option introduces variability. However, we will compute intraclass correlation by analysing session attendance patterns to see whether there is any clustering effect. If there is one, we will adjust for it using multilevel techniques.

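### Home practice is listed among subgroup analyses to be done by interaction test, but it is measured after randomisation and only in the intervention arm, so only a non-randomised within-arm slope can be estimated

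*Protocol article*

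**What the plan says.** All in the protocol article.

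- **Statistical methods.** One lead-in governs the whole list: "The following predefined subgroup analyses will be conducted on the primary outcome by using interaction tests". The items are degree, year of study, baseline CORE-OM, gender, prior meditation experience and "By amount of home practice during and after course in intervention group participants". No separate model, control-arm counterpart or caveat is given for the last of these. The primary outcome is CORE-OM in the examination period, compared between arms.
- **Outcomes and data collection, process measures.** Home practice is obtained by "asking students whether they did their mindfulness homework during the course and how much they have practised after the course". For controls, the nearest item is that "participants in the control group will be asked whether they have practised mindfulness elsewhere during the follow-up period".
- **Outcomes and data collection, baseline data.** Beyond the baseline measures in Table 1, "the following baseline data will be collected in order to compare the sample with the student population, and to run subgroup analyses"; these are prior meditation experience and registry demographics. The paragraph ends: "All baseline data will be collected before randomisation".
- **Trial design.** "Those allocated to PAU alone will be offered a mindfulness course 1 year later", so at the primary endpoint controls have had no course and no course homework.

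**The concern.** In a trial whose primary outcome is compared between arms, an interaction test for a subgroup asks whether the treatment effect differs across levels of a factor. The factor must then exist in both arms and should not be affected by allocation. Five of the six listed factors are characteristics students bring to randomisation. Home practice is not: it arises only from being given the course, and students choose how much of it to do.

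At stake is how the result may be described. The trial is meant to inform university welfare policy. A finding that students who practised more were less distressed, reported among predefined subgroup results, could be taken as effect modification or as a causal dose-response. The design does not support either reading for this variable.

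**Working it through.** The plan gives no figure for this item, so the check is structural, followed by an illustration under stated assumptions.

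**1. Is the interaction identified?** Let T be arm (0 control, 1 intervention) and P the amount of home practice. The full interaction model for CORE-OM has the columns 1, T, P and T×P. With 275 students per arm (Sample size section):

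- If P is set to 0 for every control, T×P equals P for every student. The design matrix has rank 3 with 4 columns. The redundant pair is T×P and P.
- If P is undefined in controls, only intervention students remain. T is constant, T×P again equals P, and the rank is 2 of 4.

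In neither case is there an interaction separate from the practice term.

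**2. What can be estimated?** In the first case, dropping the redundant column leaves 1, T and T×P, which can be fitted. The T×P coefficient is then the slope of CORE-OM on practice within the intervention arm. The T coefficient becomes the contrast between controls and intervention students at zero practice, which is not a randomised comparison either.

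**3. Could the control question fill the gap?** No. It asks whether mindfulness was practised elsewhere, which is a different variable from an amount of course homework, and the list item is limited to the intervention group.

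**4. What threatens the within-arm slope?**

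- *Self-selection.* The Intervention section says that extra practice is optional and suggests that students cut down when busy. Busyness could plausibly both lower practice and raise distress in the examination term.
- *Reverse causation.* Practice after the course has no stated window, so it may overlap with or follow the examination-term CORE-OM. By contrast, the per-protocol rule in Statistical methods counts controls' meditation elsewhere only up to the outcome measurement.

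**5. Illustration.** These are assumptions, not figures from the protocol. Practice has no true effect. An unmeasured factor has coefficient -0.4 on CORE-OM and correlation rho with practice; the baseline coefficient is 0.6; CORE-OM has total variance 0.36 + 0.16 + 0.48 = 1. There are 275 × 0.8 = 220 intervention completers, and 2,000 runs for each value of rho. The expected baseline-adjusted slope is -0.4 × rho.

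| rho | Expected slope (SD of CORE-OM per SD of practice) | Simulated slope | Runs significant at two-sided 0.05 |
|---|---|---|---|
| 0 | 0.00 | -0.002 | 5.3% |
| 0.1 | -0.04 | -0.041 | 11.9% |
| 0.2 | -0.08 | -0.079 | 30.7% |
| 0.3 | -0.12 | -0.119 | 60.0% |

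The false-positive rate is nominal without self-selection and rises well above 5% with modest self-selection, even after adjustment for baseline. Other assumptions would give other numbers.

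**The case against.** The strongest reply is that the lead-in does not say interaction with treatment, and that the item itself is confined to the intervention group. The authors may simply have intended a within-arm dose-response and placed it under a loose heading in a condensed article. The intention is plausible, and such a slope is estimable. But it is neither an interaction test nor a subgroup effect, and the article assigns it that test without qualification. This is a stated rule that does not fit its variable, not a detail left to an analysis plan.

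The other side is also right to resist several stronger readings that a reader might infer:

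- *That nothing can be estimated.* Only the separate interaction is lost. The reduced model runs and returns the within-arm slope.
- *That any gradient is necessarily confounded.* The documents show that it is open to confounding; they cannot show that confounding will occur.
- *That the bias would match the 0.3 SD target effect.* A median split of a normal practice variable separates the halves by 1.596 SD. An assumed correlation of 0.2 with residual distress then gives 1.596 × 0.2 = 0.32 residual SD. But correlations of 0.1 and 0.3 give 0.16 and 0.48, the plan specifies no median split, and residual SD is not the raw SD of the target. Under the simulation's assumptions the same split at rho 0.2 gives 1.596 × 0.08 = 0.13 SD. The documents support no single figure.
- *That a complier-average causal effect analysis would rescue the question.* With allocation as the instrument, it would require allocation to affect distress only through home practice. The in-class meditations, inquiry and group exercises described under Intervention make that implausible.
- *That the authors make a causal claim about practice.* They do not. Practice is classed as a process measure, and the stated limitations say that the design does not determine specific effects.

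**Conclusion.** Wrong as written, and limited in reach. The interaction test named for this item cannot be carried out as a test separate from the practice term, because practice has no values in controls. The remaining within-arm slope lacks a randomised comparator and is vulnerable to self-selection and, for practice after the course, to reverse causation. The identification result rests only on the protocol's own description of the variable and the arms. The one inference is that an interaction test on a between-arm outcome means arm by subgroup, which is the ordinary meaning. The direction and size of any bias rest on assumptions and should not be quoted as a property of the trial.

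One exploratory analysis out of six is affected. The primary intention-to-treat comparison is untouched, and this point is no objection to the other five factors.

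**What to change.** In the protocol, and in the analysis plan if the item is repeated there:

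1. Remove home practice from the subgroup list tested by interaction. Keep degree, year of study, baseline CORE-OM, gender and prior meditation experience.
2. Report home practice separately as an exploratory, non-randomised association in the intervention arm only, adjusted for baseline CORE-OM, prior meditation experience and demographics.
3. Count only practice that took place before the examination-term CORE-OM was completed.
4. State that the result will not be interpreted as effect modification or as a causal dose-response.

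The cost is wording. The covariates are already collected and practice is already asked about; the timing of that question needs only to be tied to the outcome measurement.
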